## Trial design {8}

The study is a randomised 2 × 2 factorial trial, using four conditions: IIMT, IIMT with an additional component of music listening (ML), IIMT with an additional component of vibroacoustic treatment (VAT), and IIMT with the additional elements of both ML and VAT. A superiority design is adopted with the aim of testing whether the intervention, in different conditions, demonstrates statistically and clinically superior outcomes compared with the comparator.

All sessions regardless of the condition will begin with a preparing exercise called Resonance Frequency Breathing (RFB) [24]. There will be a waiting-list control group to whom the plain IIMT will be offered after six weeks of baseline measurements, allowing a within-subject comparison between baseline and treatment conditions. Each group is offered a therapy process consisting of 12 sessions, conducted twice a week for 60 min each.

Outcomes will be measured before and after the start of the therapy and at two follow up points, 6 months and 12 months after the start of the therapy. For Condition A there will be additional baseline 2 measurements before the start of the therapy (see Fig. 1).

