#### Sample size {14}

We will recruit 200 working-age adults (18–65 years of age) suffering from one or several of the following disorders: depression (ICD-10: F32 or F33), anxiety (ICD-10: F41), or exhaustion. The sample of participants will be randomised into four groups (50 + 50 + 50 + 50) of which two groups (*n* = 100) will receive vibroacoustic treatment (VAT) and two groups (*n* = 100) not whereas two groups (*n* = 100) will receive music listening (ML) and two groups (*n* = 100) not (see Table 2).

**Table 2 Tab2:** Factorial design

	VAT yes	VAT no	
ML yes	50	50	*n* = 100
ML no	50	50	*n* = 100
	*n* = 100	*n* = 100	

For each condition, the selected sample size provided a statistical power of 0.985 for detecting a medium standardised effect size of Cohen’s d = 0.5 in a mixed-model analysis [47], with a 2-tailed significance level of *p* < 0.05 and intra-participant correlation of ρ = 0.6. For the comparison between IIMT only vs waiting-list control, the selected sample size provided statistical power of 0.9 for detecting a medium effect size (d = 0.23) in a repeated measures t-test, with a 2-tailed significance level of *p* < 0.05. These high-power levels ensure a robust detection of clinically meaningful effects, even after accounting for potential participant dropouts, while reducing the likelihood of Type II errors. Also, the selected sample sizes also retain adequate power (> 0.8) to detect smaller effects (e.g., d = 0.2), thus providing sensitivity to subtle group differences.

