## Statistical methods

### Statistical methods for primary and secondary outcomes {20a}

All statistical tests will be two-tailed with a significance level of 5%, and no adjustments will be made for multiplicity. Primary and secondary outcome measures at baseline, post-intervention, and at the first and second follow-ups will be treated as continuous dependent variables.

For the IIMT group, which also serves as the waiting-list control, we will assess clinical improvement by comparing their progress during the intervention period with that observed during the waiting period prior to treatment. Specifically, we will perform paired samples t-tests for each outcome measure, comparing the change from baseline 2 (6 weeks; pre-intervention) to post-intervention (12 weeks) against the change from baseline 1 (0 weeks; no intervention) to baseline 2 (6 weeks). Prior to analysis, we will assess the normality of the difference scores to ensure the assumptions of the t-test are met. This comparison will help isolate the treatment effect from natural fluctuations over time.

Since the participants are randomised either to the waiting list plus plain IIMT group or to one of the other three arms (B, C, and D), comparisons between plain IIMT and the waiting list are based on within-subject analyses rather than fully randomised group contrasts. No direct comparisons between the waiting list group and arms B, C, and D will be performed.

To evaluate the effects of VAT and ML on these outcomes, repeated-measures linear mixed-effects models will be applied [50]. A key advantage of this design is its ability to retain participants with missing data, ensuring that all participants contribute to the analysis. Additionally, they can account for baseline group differences, to avoid overestimating the effect size of treatment. VAT and ML will be included as fixed effects, with a random intercept for each participant to account for the dependency of repeated measurements. To control for baseline differences across conditions, treatment terms will be omitted from the model, allowing the effects of VAT and ML to be estimated through their interactions with time. As an exploratory analysis, the models will be extended to include a VAT × ML interaction term to examine potential synergistic effects between the two interventions.

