In addition to evaluating treatment effects post-intervention and at follow-up time points, we will calculate an overall treatment effect over time (denoted as *B*). This will represent the raw mean difference associated with the presence versus absence of each factor. *B* will be derived by summing the regression coefficients corresponding to each condition across all time points [28]. To estimate effect sizes for each outcome, the overall treatment effect over time will be divided by the baseline standard deviation of the respective measure across all participants.

For each participant, a dichotomous treatment response variable will be calculated, defined as a reduction of at least 50% in CORE-OM scores between the baseline and post-intervention assessments. Fisher’s exact test and odds ratios will be calculated separately for VAT and ML. For statistically significant effects, clinical significance will be assessed by calculating the risk difference and the number needed to treat (NNT).

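### Risk difference and NNT are calculated only for significant effects, so the absolute benefit is overstated on average when reported and is not planned otherwise

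*Protocol article*

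**What the plan says.** The point is in the protocol article, Statistical methods for primary and secondary outcomes {20a}. A participant is a responder if there is a change "defined as a reduction of at least 50% in CORE-OM scores between the baseline and post-intervention assessments". For this outcome, "exact test and odds ratios will be calculated separately for VAT and ML". The next sentence sets the rule at issue: "For statistically significant effects, clinical significance will be assessed by calculating the risk difference and the number needed to treat".

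Other effect measures in the same section carry no such condition. The odds ratios just mentioned are one. The overall effect B, a raw mean difference, is another. So are the standardised effects: "To estimate effect sizes for each outcome, the overall treatment effect over time will be divided by the baseline standard deviation". The error rate is also fixed there: "All statistical tests will be two-tailed with a significance level of 5%, and no adjustments will be made for multiplicity".

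Trial design {8} describes a superiority trial that asks whether the intervention "demonstrates statistically and clinically superior outcomes compared with the comparator".

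**The concern.** How large an effect is and whether it differs from zero are separate questions. The rule makes the answer to the first depend on the second. A risk difference that appears only after passing a significance test comes from the upper part of its sampling distribution, so its average lies above the true value, and the corresponding NNT looks too favourable. A factor that misses significance gets no planned risk difference, so a reader cannot tell on the absolute scale whether its effect is negligible or merely imprecise.

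The protocol makes the risk difference and NNT its assessment of clinical significance, and the trial aims to address clinical as well as statistical superiority. VAT and ML are components of about 15 minutes added to a therapy that every arm receives, so modest differences in response are plausible. Those are the cases in which the selection matters most.

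**Working it through.** **Inputs from the protocol**
- Sample size {14}: "The sample of participants will be randomised into four groups (50 + 50 + 50 + 50"), which gives 100 v 100 for each factor.
- Two-sided 5% with no multiplicity adjustment ({20a}).
- Early leavers are counted as non-responders ({20c}), so the denominators stay at 100.

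**Assumptions**
- The gate is Fisher's test. The text does not name it, but the sentence directly follows the one on Fisher's test.
- The comparator responder rate is 20%, 30% or 40%, and the true risk difference (RD) runs from 0 to 0.30. The protocol gives no responder rates.

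**The plan's own power figure.** Sample size {14} states that "the selected sample size provided a statistical power of 0.985 for detecting a medium standardised effect size of Cohen’s d = 0.5", with a within-participant correlation of 0.6. Take the mean of three post-baseline measures under compound symmetry:
- SD factor = √((1 + 2×0.6)/3) = 0.856
- effective d = 0.5/0.856 = 0.584
- 0.584 × √(100/2) = 4.13
- power ≈ Φ(4.13 − 1.96) = 0.985

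The stated figure reproduces at 100 v 100, which supports using that comparison here. It concerns the continuous outcome. The protocol states no power for the responder analysis.

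**Selection on significance.** Let X₁ ~ Bin(100, p₀ + RD) and X₀ ~ Bin(100, p₀). Every table (x₁, x₀) is enumerated and marked significant if the two-sided Fisher p ≤ 0.05. The mean reported value is E[(X₁ − X₀)/100 | significant, X₁ > X₀].

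Results for comparator rates of 20% / 30% / 40%:

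| True RD | P(significant) | Mean reported RD | Ratio to truth |
|---|---|---|---|
| 0.05 | 0.10 / 0.09 / 0.09 | 0.153 / 0.170 / 0.177 | 3.06 / 3.40 / 3.54 |
| 0.10 | 0.31 / 0.26 / 0.26 | 0.169 / 0.183 / 0.187 | 1.69 / 1.83 / 1.87 |
| 0.15 | 0.61 / 0.54 / 0.53 | 0.189 / 0.200 / 0.202 | 1.26 / 1.34 / 1.35 |
| 0.20 | 0.84 / 0.79 / 0.79 | 0.218 / 0.225 / 0.226 | 1.09 / 1.12 / 1.13 |
| 0.25 | 0.96 / 0.94 / 0.94 | 0.256 / 0.259 / 0.259 | 1.02 / 1.04 / 1.04 |
| 0.30 | 0.99 / 0.99 / 0.99 | 0.301 / 0.302 / 0.302 | 1.00 / 1.01 / 1.01 |

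With a 30% comparator and a true RD of 0.10, the true NNT is 1/0.10 = 10, but the mean reported RD implies 1/0.183 = 5.5. In that row 69–74% of analyses (1 − 0.31 to 1 − 0.26) are not significant and would yield no RD. With no true effect, the 3–4% of analyses that are significant show a mean absolute RD of 0.14–0.17.

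**Smallest reportable RD.** The first significant tables are:
- 34 v 20 responders: RD 0.14, NNT 7.1
- 45 v 30: RD 0.15, NNT 6.7
- 55 v 40: RD 0.15, NNT 6.7

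This floor depends on the observed comparator count. At 10 responders it is 21 v 10, RD 0.11, NNT 9.1.

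**With the condition removed.** E[RD] equals the true RD in every scenario (ratio 1.00).

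**The case against.** A reader might infer that every clinical-effect figure in the report will be selected on significance, or that a non-significant factor will come with no estimate at all. The text does not support either reading. Odds ratios, B and standardised effects are planned without a significance condition, and only the risk difference and NNT are gated. The risk difference can also be worked out from the four responder counts, if these are published.

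This narrows the point but does not remove it. An odds ratio does not give the absolute benefit unless the comparator risk is known. For 44 v 30 responders, one short of significance, the odds ratio is (44×70)/(56×30) = 1.83 and the RD is 0.14. With a comparator risk of 10%, the same odds ratio gives odds of 0.111×1.83 = 0.204, a risk of 0.169 and an RD of about 0.07.

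A second tempting reading is that each reported figure will be too large. The inflation is an average. At a true RD of 0.20 about 33–37% of significant results understate it, and at 0.30 about 46% do. The design's main target is d = 0.5. Under a normal shift from a 30% responder rate this is Φ(−0.524 + 0.5) = 49%, an RD of about 0.19, where the average inflation is mild. The protocol also claims sensitivity to d = 0.2, however. The same shift gives Φ(−0.524 + 0.2) = 37%, an RD of about 0.07, where the inflation is large.

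Third, the trial design section does not define clinical superiority by the risk difference or NNT, so the two sections do not contradict each other. The responder analysis supplements a continuous primary outcome.

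Finally, withholding the NNT for a non-significant effect is defensible, because its interval then passes through infinity. That argument does not extend to the risk difference.

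**Conclusion.** The point holds for the risk difference and NNT only. It is a rule stated in the protocol, not a detail left to an analysis plan. The bias is upward on average. Over comparator rates of 20–40% it is about 1.7 to 1.9 times at a true RD of 0.10, about 1.3 times at 0.15, about 1.1 times at 0.20, and negligible from 0.25 upwards. These sizes rest on assumed responder rates and on Fisher's test being the gate. A gate based on the mixed model would select differently, and probably less strongly, on the risk difference. The primary test, the primary estimate, the sample size and the power are unaffected, so this is a minor but worthwhile correction.

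**What to change.** In {20a}, strike the introductory phrase that limits the sentence to significant effects. State that the risk difference, with its 95% confidence interval, will be reported for VAT and for ML whatever the p-value. The NNT may be kept as an optional addition where that interval excludes no effect.

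The cost is a change of wording and at most two more table rows. No further data are needed. Recruitment is expected to run until the end of December 2028, so the change can be made well before the final analysis.

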### Interim analyses {21b}

Not applicable, no interim analysis included.

### Methods for additional analyses (e.g. subgroup analysis) {20b}

In addition to the primary efficacy analysis, an adjusted efficacy analysis and two sensitivity analyses will be conducted. Each repeated-measures linear mixed-effects model for continuous outcomes will be adjusted for the following prognostic covariates: age group (18–34, 35–49, 50–65), gender, medication use (antidepressants, anxiolytics, or hypnotics). Therapists will be added as random effects. Model fit will be assessed through the Akaike Information Criterion (AIC) and Bayesian Information Criterion (BIC). The covariates that optimise these criteria will be retained in the final model. Two sensitivity analyses will be performed for the primary outcome: (1) a single imputation method using Last Observation Carried Forward (LOCF), which assumes no change for missing data, and (2) an analysis based on treatment as received.

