#### Participant timeline {13}

There are overall four to five testing timepoints in this study: during the recruitment of the participants (baseline), 6 weeks after the beginning of the intervention (post-intervention), 6 months after the beginning of the intervention (first follow-up) and 12 months after the beginning of the intervention (second follow-up). The waiting-list control group will have an additional testing timepoint (baseline 2) at 6 weeks after the initial baseline tests before starting the therapy. This will also act as a new baseline for the intervention.

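### LOCF, the only sensitivity analysis for missing CORE-OM scores, is a single implausible departure from missing at random and says little about whether the primary result is robust

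*Protocol article*

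**What the plan says.** Protocol section {20a} analyses CORE-OM with a linear mixed model that has a random intercept per participant and uses all available data. It covers four visits: "Primary and secondary outcome measures at baseline, post-intervention, and at the first and second follow-ups will be treated as continuous dependent variables". On the model terms it says: "treatment terms will be omitted from the model, allowing the effects of VAT and ML to be estimated through their interactions with time". Section {20c} adds an intention-to-treat rule with no imputation of continuous outcomes.

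Section {20b} then gives a closed list of two sensitivity analyses for the primary outcome. The first is "a single imputation method using Last Observation Carried Forward (LOCF), which assumes no change for missing data". The second analyses participants by the treatment they received, which concerns adherence rather than missing scores. Section {20c} counts early leavers as failures on dichotomous variables, but that is the main rule for those variables, not a check on the continuous CORE-OM result. Section {18b} states that no data are gathered after a participant discontinues the study.

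**The concern.** A likelihood-based mixed model on available data is valid if scores are missing at random. Leavers are not followed, so the data cannot confirm this. The job of a missing-data sensitivity analysis is to show how far the assumption can fail before the conclusion changes.

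LOCF does not do that. It swaps the assumption for one fixed alternative and varies nothing. By the protocol's own description that alternative is an absence of change, yet section {11a} gives IIMT in all four conditions and the Discussion expects participants to improve. A participant lost before the post visit is frozen at baseline. One lost later is frozen at the last on-treatment score. The filled-in values are then analysed as if they had been observed.

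At stake is how the CORE-OM result is described. A comparison with LOCF could make a sound result look fragile, or a fragile one look sound.

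**Working it through.** **Inputs from the protocol.** 200 participants in four groups of 50, so 100 v 100 for each factor; "intra-participant correlation of ρ = 0.6"; two-sided 5% without multiplicity adjustment; baseline plus three later visits.

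**Inputs assumed.** Dropout and mean improvement, because the documents give no figure for either. Effects are in baseline SD, and negative values mean benefit.

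**Step 1: reproduce the plan's own figure.** Section {14} says "the selected sample size provided a statistical power of 0.985 for detecting a medium standardised effect size of Cohen’s d = 0.5".
- SD of the mean of three post-baseline scores: √((1 + 2 × 0.6)/3) = 0.856.
- SE of the difference: 0.856 × √(2/100) = 0.121.
- Power: Φ(0.5/0.121 − 1.96) = Φ(2.17) = 0.985.

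The figure reproduces, so the 100 v 100 comparison with correlation 0.6 is a fair base for what follows.

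**Step 2: size by arithmetic.** Suppose no true effect, an improvement of m at every visit, and dropout unrelated to the scores. LOCF then shifts the factor effect by about (difference in the proportion lost before the post visit) × m.
- 10-point gap, all loss before the post visit: 0.10 × 0.5 = 0.05 SD to 0.10 × 0.8 = 0.08 SD.
- 10-point gap, loss spread evenly over the three intervals: 0.10/3 = 0.033 is lost before the post visit, so 0.033 × 0.5 = 0.017 to 0.033 × 0.8 = 0.027 SD.

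With equal 20% loss and a true effect of 0.5 SD:
- All loss before the post visit: 0.5 × (1 − 0.20) = 0.40.
- Loss spread evenly: 0.5 × (1 − 0.20/3) = 0.467.

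**Step 3: the planned model.** 3,000 simulated trials per setting, N = 200, four visits, correlation 0.6, improvement of 0.5, 0.6 and 0.6 SD at the three later visits, and dropout accumulating to 12 months. The model has time, VAT × time and ML × time, without treatment main effects. Results are for VAT; ML is symmetric. Average means the mean over the three later visits.

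| Dropout, no VAT v VAT | True effect | Mixed model, average | LOCF, average | LOCF, 12 months | LOCF rejection rate, average / 12 months |
|---|---|---|---|---|---|
| 5% v 15%, MCAR | 0 | 0.00 | +0.023 | +0.025 | 7.3% / 5.5% |
| 10% v 30%, MCAR | 0 | 0.00 | +0.050 | +0.052 | 10.6% / 8.0% |
| 30% v 10%, MCAR | 0 | 0.00 | −0.047 | −0.053 | 10.1% / 8.1% |
| 10% v 30%, MAR | 0 | 0.00 | +0.073 | +0.087 | 15.3% / 13.9% |
| 20% v 20%, MCAR | 0 | 0.00 | 0.00 | 0.00 | 6.7% / 5.9% |
| 20% v 20%, MCAR | −0.5 | −0.50 | −0.463 | −0.463 | – |
| 10% v 30%, MCAR | −0.5 | −0.50 | −0.397 | −0.393 | – |
| 10% v 30%, MNAR | 0 | −0.042 | +0.037 | +0.041 | 9.9% / 8.4% |

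In the MCAR and MAR rows with no true effect, the mixed model rejects in 4.7% to 5.3% of trials. In the 10% v 30% row with a true effect of −0.5, 12-month interval coverage is 81.5% for LOCF and 94.6% for the mixed model.

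**Step 4: precision.** At 20% v 20% with no effect, the LOCF model SE of the average effect is 0.084. That is below the 0.086 obtained with complete data, while the estimate's actual SD is 0.089. There is no bias in this row, so the 6.7% rejection rate comes from the small SE.

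**The case against.** The best defence has four parts.

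- **LOCF has no deciding role.** Section {20b} attaches no decision rule to it, and the primary analysis is the mixed model. This stands. A reader might infer that the trial's type I error is inflated, or that the conclusion will be accepted or rejected on LOCF. The documents say neither.
- **The effect may be small.** The Discussion reports low dropout in the team's earlier trials, without a figure. At 5% v 15% spread over the visits the shift is only about 0.02 SD. This stands as a limit on size.
- **LOCF does depart from missing at random, so it is not empty.** In the one MNAR setting tried, the two analyses fell on either side of the truth. So it would be too strong to say that LOCF cannot test the primary result. But bracketing in one setting is no guarantee, and a reader of the real results could not tell which analysis had moved.
- **A tipping-point series is often left to the SAP.** True of detail, but here the article itself names the method.

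Three stronger readings are tempting and are not supported.

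- **Waiting-list loss favours VAT and ML.** The waiting-list arm sits in both the no-VAT and no-ML groups, and its post score comes at 12 weeks: "The waiting-list control group will have an additional testing timepoint (baseline 2) at 6 weeks after the initial baseline tests". But if the other arms lose 15%, factor-level losses of 20%, 25% and 30% need 25%, 35% and 45% in that arm (for example, (25 + 15)/2 = 20). Nothing in the documents suggests this. Section {13} also makes the second measurement the starting point for therapy in that arm, leaving six weeks to the post score.
- **LOCF scores every leaver as unimproved.** This is true only of those lost before the post visit.
- **LOCF overstates precision in any model.** With a single post score analysed by ANCOVA and 15% loss in both groups, the LOCF SE is 0.114 against 0.123 for observed cases, but it matches its own sampling SD. The fault shows only in the repeated-measures model.

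**Conclusion.** The point holds, confined to the robustness check. LOCF can depart from the truth when the planned mixed model is exactly right, under both MCAR and MAR, and it does not explore a range of departures from missing at random. Comparing the two therefore tells the reader little in either direction.

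The size is modest under mild dropout: hundredths of an SD for a 10-point gap, with the timing of loss deciding where in the 0.02 to 0.08 SD range it falls. It grows with a wider gap, or when dropout depends on observed scores. Shrinkage of a true effect needs no imbalance at all. All of this rests on assumed dropout, improvement and a compound-symmetry correlation of 0.6; only the last figure comes from the protocol. The primary estimate and its error rate are not called into question.

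**What to change.** In section {20b}, replace sensitivity analysis (1) with a delta-adjusted multiple-imputation series for CORE-OM:

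- Impute missing scores under missing at random (delta = 0). This step alone largely repeats the mixed model, so it serves as the anchor and not as the check.
- Add a delta to the imputed scores over a grid fixed in advance, varied separately by level of VAT and by level of ML.
- Report the delta at which the CORE-OM conclusion for each factor changes, so that readers can judge whether such a departure is plausible.

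LOCF may stay as a descriptive extra if comparability with earlier work is wanted, but should not be offered as evidence of robustness. The cost is some extra programming in standard software, with no new data or participants. Recruitment is planned to run to the end of 2028, so the change can still be specified in advance.
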